## Abstract

**Background:**

Children with haemophilia have lower levels of fitness and strength than their healthy peers. We present the protocol of a study designed to determine whether an exercise intervention improves quality of life, aerobic fitness and strength in children with haemophilia.

**Methods/Design:**

The study will be a randomised, assessor-blinded, controlled trial of exercise treatment. Seventy children aged between 6 and 18 years with haemophilia or von Willebrand disease will be recruited from two paediatric haemophilia clinics in NSW. Each participant will be allocated to an exercise group or a control group using a concealed allocation procedure. The control group will receive usual medical care while the intervention group will receive usual medical care plus an exercise program for 12 weeks. Outcomes (VO_2peak_, knee extensor strength and quality of life) will be measured at baseline and on completion of the exercise program by a blinded assessor. The primary analysis will be conducted on an intention to treat basis. The effects of the exercise intervention on each of the three primary outcomes will be estimated from between-group differences in the mean outcome adjusted for baseline scores.

**Discussion:**

This study will be the first randomised controlled trial to examine the effects of a structured exercise program on fitness and quality of life in children with haemophilia.

The therapeutic role of exercise in children with haemophilia has not been well documented but there is some evidence that exercise can improve coagulation parameters. Factor VIII levels have been shown to increase after a single strenuous bout of exercise in non-haemophiliacs [5,6]. A modest improvement in coagulation parameters after an acute bout of exercise has also been shown in children with mild and moderate haemophilia [7]. Whether this improvement in coagulation parameters correlates with frequency and severity of bleeding episodes remains unclear. One pilot study which examined the effect of resistance training on 5 adults with haemophilia reported this type of training improved strength and reduced the frequency and severity of bleeding episodes [8]. However, the findings of this small and uncontrolled study cannot be considered reliable. The effects of resistance training on frequency and severity of bleeds needs to be tested in a larger randomised controlled trial.

Studies which report positive effects from an exercise intervention in adults with haemophilia have had very small subject numbers and lacked experimental controls [8]. Hilberg et al. [9] documented improvements in isometric leg strength and proprioception in *adults *with severe haemophilia following a physical training programme, but this study had small numbers and was not randomised and therefore gives limited information about the effect of exercise on muscle performance.

Finally, the effect of an exercise programme on quality of life in children with haemophilia has yet to be examined. In other chronic diseases in children, however, exercise interventions have shown positive effects on quality of life. Selvadurai et al. [10] reported improvements in quality of life, as measured by the Quality of Well Being Scale, in children with cystic fibrosis following an in-hospital aerobic exercise programme. Recently a disease-specific quality of life questionnaire (Haemo-QoL) has been validated in children with haemophilia [11-13]. The effect of an exercise programme on quality of life can now be assessed.

The primary aim of this study is to determine the effects of exercise on aerobic fitness, strength and quality of life in children with haemophilia. A secondary aim is to examine the effect of an exercise programme on the frequency and severity of bleeding episodes.

## Study design

This study will be a randomised, assessor-blinded, controlled trial of exercise treatment for children with haemophilia. The control group will receive usual medical care while the intervention group will receive a general exercise program of 12 weeks duration. Outcomes will be measured at baseline, on completion of the exercise program at 3 months and at 6 months.

Seventy children with Haemophilia A or B or von Willebrand disease who are currently managed through the haematology clinic at The Children's Hospital at Westmead and Sydney Children's Hospital will be recruited. To participate in the study children must be aged between 6 and 18 years, have a diagnosis of mild, moderate or severe haemophilia (A or B) or von Willebrand disease and the parent/guardian and child must agree to accept randomisation to either intervention or control group. Subjects will be excluded if they have any contraindication to aerobic or resistance training. Children who are already involved in regular, organised physical activity lasting greater than 1 hour for more than 3 sessions per week will also be excluded.

## Methods

Following the screening consultation, baseline measures will be collected by the researcher. All children will have baseline anthropometric data recorded (height, weight, BMI, and body fat using bioelectrical impedance). They will then undergo fitness testing. This will consist of tests of grip strength and isokinetic strength testing to assess quadriceps and hamstrings strength in the non-dominant leg. In addition a VO_2peak _test will be performed using a treadmill protocol. All subjects or their parents/guardians will complete the Haemo-QoL questionnaire [13] and the Habitual Activity Estimation Scale (HAES) [14]. The HAES questionnaire will be used to explain effects of exercise, should they be apparent, and to determine whether completing a structured 12 week exercise program increases levels of habitual activity.

A randomisation schedule will be created with computer-generated random numbers by a person not otherwise involved in the recruitment process. The allocation will be in randomly permuted blocks of 4, 6 and 8. Allocations will be placed in sequentially numbered, sealed, opaque envelopes to ensure concealment from the researchers recruiting subjects, and from the subjects themselves, prior to randomisation. Potential subjects (or the guardians of subjects) will be invited to participate in the study and the methods of the study will be explained to them verbally and in writing. If they agree to participate baseline measures will be obtained before the subject is randomised to a group. Subjects will be considered to have entered the trial at the time the envelope containing their allocation is opened.

Participants in the **control group **will receive usual medical care by their treating haematologist and associated health practitioners. Their management will include factor therapy (prophylaxis or "on demand"), as determined by their treating haematologist. All parents will have been educated about the disease and been taught how to recognise a bleeding episode. For the purposes of this study when defining a bleeding episode we have accepted the definition widely used by other researchers that is, a bleed is "an episode of bleeding requiring treatment with clotting factor"[15]. Parents will be encouraged to treat bleeding episodes as soon as recognized and advice about duration of therapy will be given by their treating haematologist.

Participants in the **exercise group **will receive a supervised, general exercise program in addition to their usual medical care. The exercise program will be conducted for 1 hour, two times per week for 12 weeks. The program will consist of a supervised "circuit training" programme including warm-up and warm-down and an age-appropriate mix of resistance exercises and aerobic stations. Aerobic training will consist of 30 minutes of continuous exercise at 60–70% HR_max_, depending on baseline fitness of the participant, as measured by VO_2peak _test. Resistance training will follow the traditional "set system" and involve 20 minutes of upper and lower limb exercises using isotonic pin-loaded equipment. The training load will be set at the 8–12 repetition maximum (RM). Subjects will perform 3 sets, each to failure, with the 8–12 RM load. Throughout the training period the load will be incremented so that failure occurs at between 8 and 12 repetitions. Ten minutes per session will involve warm-up and warm-down exercises[16]. The exercise sessions will be changed frequently to avoid boredom. Patients receiving prophylactic Factor VIII will administer this prior to the exercise intervention. A qualified paediatric physical therapist will conduct and supervise the exercise program. The therapist will undergo additional training in the aetiology and management of haemophilia and understand the early management of a bleeding episode.

Participants in the control group will be advised not to change their physical activity levels during the course of the trial. In cases where this is unavoidable, a record of the changes will be kept. Several mechanisms will be used to ensure that the trial protocol is consistently applied. Protocol manuals will be developed and the researchers (haematologists, physical therapists, exercise physiologists, other outcome assessors and the trial manager) will be trained to ensure that screening, outcome assessment, allocation and treatment protocols are conducted according to the protocol. An independent researcher will randomly audit assessment and treatment sessions to determine adherence to the protocol. Retraining will be offered to treatment providers and outcome assessors not complying with the protocol.

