### Sample size and power analysis

A sample size of 70 subjects (35 subjects per group) will provide an 80% probability of detecting an effect of 0.75 standard deviations on H-QOL scale assuming α of 0.05 and worst-case loss to follow up of 15%.

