### Data analysis

Data will be analysed by a statistician who is blinded to group. All analyses will be by intention to treat. That is, outcome data will be collected regardless of compliance with the trial protocol, and each patient's data will be analysed in the group to which the subject was allocated. The effect of exercise will be estimated with analysis of covariance using a regression approach. To maximise the precision of estimates, pre-test scores of outcome variables will be entered into the regression models as covariates. The uncertainty associated with estimates of the size of effects of exercise will be quantified with 95% confidence intervals. The integrity of the trial data will be monitored by regular scrutiny of data sheets for omissions and errors. Data will be double entered and the source of any inconsistencies will be explored and resolved.

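### The analysis names no covariate but the pre-test score, so the bleeding comparison goes unadjusted for disease severity and the three primary analyses forgo a modest gain in precision

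*Protocol article*

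**What the plan says.** The Protocol article describes allocation under Methods: "A randomisation schedule will be created with computer-generated random numbers by a person not otherwise involved in the recruitment process", and "The allocation will be in randomly permuted blocks of 4, 6 and 8". Concealment is by numbered opaque envelopes. Neither hospital, severity, diagnosis nor age is named as a stratification factor.

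Under Data analysis, "The effect of exercise will be estimated with analysis of covariance using a regression approach". To gain precision, "pre-test scores of outcome variables will be entered into the regression models as covariates". No further covariate is named there, and the Abstract likewise mentions baseline scores alone.

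The population is mixed. Two hospitals recruit children from 6 to 18 years old who "have a diagnosis of mild, moderate or severe haemophilia (A or B) or von Willebrand disease" (Study design). The Background says that the severity of the bleeding tendency depends on the factor level, and that mild disease seldom leads to spontaneous bleeds. It gives bleeding frequency and severity as the secondary aim. Under Outcomes, bleeds are counted for 16 weeks from the start of the intervention. The baseline measures listed under Methods include no count of earlier bleeds.

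**The concern.** Blocking keeps the arm sizes close. It does nothing for the make-up of the arms, and with 35 children per arm severity or age can differ noticeably by chance.

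For the primary outcomes the pre-test score carries part of any such imbalance, and the ANCOVA removes that part. For bleeds the plan describes no pre-test score. Followed as written, it compares bleeding without adjusting for the prognostic factor that the article itself identifies. An uneven split of severe children could then look like a harm or a benefit of exercise. If severity were added only after the split was seen, the adjustment would be open to the charge of being post hoc.

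**Working it through.** **1. The plan's own figure.** The article states 35 per group, two-sided or one-sided not specified, alpha 0.05 and 15% loss, which "will provide an 80% probability of detecting an effect of 0.75 standard deviations on H-QOL scale". A two-sided two-sample t-test (noncentral t) needs 29 per group. Then 29 / (1 − 0.15) = 34.1, rounded up to 35, or 70 in all. The figure reproduces and relies on no covariate.

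**2. Primary outcomes.** Let q be the share of residual variance, after the pre-test score, that the added covariates explain. The standard error is multiplied by √(1 − q). The documents give no value for q or for the pre-post correlation r, so both are assumed. Evaluable children per group: 35 × 0.85 = 29.75.

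| q | √(1 − q) | Fall in SE | Power at 0.75 SD, r = 0.3 | r = 0.5 | r = 0.7 |
|---|---|---|---|---|---|
| 0 | 1.000 | none | 84.6% | 90.7% | 97.8% |
| 0.05 | 0.975 | 2.5% | 86.3% | 92.0% | 98.3% |
| 0.10 | 0.949 | 5.1% | 88.0% | 93.2% | 98.7% |
| 0.20 | 0.894 | 10.6% | 91.4% | 95.6% | 99.3% |

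The rows with q above 0 charge five extra degrees of freedom, more than age and severity need. The required sample size does not change.

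**3. How often severity is uneven.** Assume that 25 of 70 children are severe. With 35 per arm, the hypergeometric probability that the arms differ by 5 or more severe children is 0.318. Simulating blocks of 4, 6 and 8 gives 0.319. For assumed totals of 15 to 35 severe children the probability is 19% to 34%.

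**4. What a 15 to 10 split does to bleeds.** One arm has 15 severe and 20 other children, and the other has 10 and 25. Exercise is taken to have no effect. Other children are assumed to have 0.5 bleeds per 16 weeks, and the rate in severe children is varied.

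| Bleeds per severe child | Arm with 15 severe | Arm with 10 severe | Rate ratio |
|---|---|---|---|
| 4 | 15×4 + 20×0.5 = 70 | 10×4 + 25×0.5 = 52.5 | 1.33 |
| 2 | 30 + 10 = 40 | 20 + 12.5 = 32.5 | 1.23 |
| 1.5 | 22.5 + 10 = 32.5 | 15 + 12.5 = 27.5 | 1.18 |
| 1 | 15 + 10 = 25 | 10 + 12.5 = 22.5 | 1.11 |

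Either arm may hold the excess, so the ratio may run in either direction.

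**5. What stratified envelopes would cost.** With one schedule, the arm totals differ by 0.6 children on average in simulation (95th percentile 2). Stratifying by hospital alone gives 1.1 (95th percentile 2). Crossing two hospitals with four severity or diagnosis groups, assumed equal in size, gives 2.4 (95th percentile 6), because many blocks stay incomplete.

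**The case against.** The best case on the other side is that nothing here is wrong. Concealed permuted blocks with a baseline-adjusted ANCOVA are a sound design. Chance imbalance causes no bias on average and does not inflate the type I error, and ordinary confidence intervals already allow for it. The pre-test score absorbs much of what age and severity contribute to the primary outcomes. The article is also condensed, and further covariates are often left to an analysis plan. All of this stands, and it confines the point to efficiency and to one secondary outcome.

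Three stronger readings are tempting, and the documents do not support them:

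- **That the trial is declared unstratified and adjusted for the pre-test score alone.** The article never says either. It names no stratification factor and no other covariate, which is silence and not exclusion.
- **That the bleeding result would be off by a third.** The ratio of 1.33 needs an assumed 25 severe children, an unlucky split and an assumed eightfold contrast in rates. Usual care includes prophylaxis, which could narrow that contrast, and at 1 to 2 bleeds per severe child the ratio is 1.11 to 1.23.
- **That stratification would cost nothing and should be required.** At 70 children, fine strata loosen the balance of arm totals, so it is a trade-off.

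The objection does not dispose of the bleeding analysis. The one adjustment that the article states cannot apply where no baseline count is described, and the article itself says why severity matters there.

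**Conclusion.** The point holds as an improvement to the stated model and not as an error. For the three primary outcomes it is minor: the standard error would fall by 2.5% to 11% if the added covariates explained 5% to 20% of the residual variance, and the stated power does not depend on it. For bleeding it carries more weight. A 15 to 10 split of 25 severe children would give an expected null rate ratio of about 1.1 to 1.3, and a difference of that size or larger between the arms has a probability of about 32%. The number of severe children and the bleed rates are assumptions. The link between factor level and bleeding, and the absence of a listed baseline bleed count, come from the article.

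**What to change.** In Data analysis, prespecify disease severity (severe versus other) and hospital as covariates in the model for the bleed rate. In the ANCOVAs, add age and severity to the pre-test score. The article defines severity grades only for haemophilia, so the plan should say in advance on which side children with von Willebrand disease are counted. The choice should be recorded before outcome data by group are seen.

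All three factors are known before randomisation, so no new data are needed. The cost is two degrees of freedom per model. In the ANCOVAs that is 2 of about 56.5 (2 × 29.75 = 59.5 evaluable children, less 3). The envelopes can stay as they are. If the sponsor wants to stratify, hospital alone is the inexpensive choice, but the fix does not require it. The article could also state whether hospital or severity plays any part in allocation.

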### Outcomes

The primary outcomes will be quality of life, strength and aerobic fitness. The details are as follows:

1. **Quality of Life **using the Haemo-QoL questionnaire. This questionnaire has been validated in children with haemophilia [13]

2. **Quadriceps strength **using a Cybex isokinetic dynamometer [17]

3. **VO_2peak _**using the Bruce treadmill protocol [18]

The *secondary *outcomes are as follows:

1. **Incidence of haemarthroses and intramuscular bleeds **– self-reported for 16 weeks (12 week intervention period and 4 weeks following)

2. **Lean tissue mass, body fat **measured using bioelectrical impedance on a body composition analyser

3. **Habitual activity **using HAES questionnaire [14]

4. **Other strength measures**

- Isokinetic hamstrings strength using a Cybex isokinetic dynamometer

- Grip strength using a hand dynamometer [19]

5. **Adverse events **(other than haemarthroses) associated with exercise or physical activity. These will be elicited by open-ended questioning.

All measurements will be taken immediately after the 12 week intervention period, by an assessor blind to group allocation. (The exception is measurement of bleeding episodes, which will be monitored as described above.) Habitual activity and quality of life will be re-measured in a telephone interview at six months. The number and type of any adverse effects that occur for the duration of the study will also be recorded using open-ended questioning.

In order to improve compliance and reduce loss to follow-up, participants in the intervention and control groups will be telephoned at the beginning of each week. Participants in the both groups will be asked about bleeding episodes in the previous week. In addition, participants in the intervention group will be reminded of their exercise training schedule. All participants will be asked to keep a diary to record all bleeding episodes during and for one month following the intervention period. The final data on number of bleeds will be a composite of the data obtained from diaries and from telephone follow-ups.

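### The timing of adverse-event questioning is unsettled and the weekly calls and diary are described for bleeding only, so other injuries may rest on recall and be ascertained unequally between arms

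*Protocol article*

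**What the plan says.** All of this is in the Outcomes section of the protocol article unless stated otherwise.

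- **Outcome.** Secondary outcome 5 is adverse events, haemarthroses excluded, that are linked to exercise or physical activity. The method is "These will be elicited by open-ended questioning". The item gives no date or frequency.
- **Timing rule.** "All measurements will be taken immediately after the 12 week intervention period, by an assessor blind to group allocation". One exception follows: "The exception is measurement of bleeding episodes, which will be monitored as described above".
- **Recording period.** After a sentence on a six-month telephone interview, which names habitual activity and quality of life, the section adds: "The number and type of any adverse effects that occur for the duration of the study will also be recorded using open-ended questioning". No contact is named.
- **Weekly calls.** "participants in the intervention and control groups will be telephoned at the beginning of each week". On safety: "Participants in the both groups will be asked about bleeding episodes in the previous week". In one arm only, "participants in the intervention group will be reminded of their exercise training schedule".
- **Diary.** "All participants will be asked to keep a diary to record all bleeding episodes", through the intervention and for a month after it. Diary and call data are merged into the bleed count. Nothing similar is described for adverse events.
- **Other contact (Methods section).** The exercise arm has one-hour sessions twice a week for 12 weeks, supervised by a paediatric physical therapist. The control arm has usual care. The same section counts a bleed only if it was treated with clotting factor.

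**The concern.** Outcome 5 is the only listed outcome that captures non-bleeding harm from a loaded exercise programme in children with a bleeding disorder. A strain, a fall or a minor bleed not treated with factor lies outside the bleed count as defined, so it can reach the trial data only by the adverse-event route.

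That route is less well fixed than the one for bleeds. The single exception puts the questioning at week 12, while the later sentence extends recording to the whole study without saying who asks, or when. Meanwhile the trial already has a weekly contact and a diary in both arms, and describes neither as asking about anything but bleeding.

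Two things are at stake. Minor and moderate events early in the 12 weeks may not be recalled at the end. And because one arm is seen by a therapist twice a week and the other is not, the chance that an event comes to light may differ by arm, so the between-group comparison of harms could be distorted.

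**Working it through.** **Step 1. Set the sentences side by side.**

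| Element | Bleeding | Other adverse events |
|---|---|---|
| Exempt from the week-12 rule | Yes, the only exception | No |
| Named content of the weekly call | Yes, both arms | Not named |
| Named content of the diary | Yes, both arms | Not named |
| Period covered | 16 weeks | Whole study |
| Contact at which the question is put | Weekly | Not stated beyond the week-12 rule |

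If the single exception governs, adverse events are asked about at week 12. If the whole-study sentence means continuing enquiry, adverse events are a second exception and the timing rule is wrong. If it means only that the period is long, the enquiry is still retrospective. On every reading, no regular contact is named at which both arms are asked about non-bleeding injuries.

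**Step 2. Count the contacts by arm.** Over the intervention the exercise arm has 2 × 12 = 24 supervised sessions. The control arm has none. Weekly calls are common to both arms.

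**Step 3. Size of equal under-recall (illustration).** The documents give no adverse-event rate and no recall fraction, and the plan has no figure of its own to reproduce on this point. From the sample-size section I take only 35 per arm; that number does reproduce (29 per arm by t-test for 0.75 SD and 80% power; 29/0.85 = 34.1, rounded up to 35). The risks below are assumptions.

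With true risks p0 (control) and p1 (exercise) and a recall fraction s equal in both arms, the observed risks are s·p0 and s·p1, and the observed difference is d = s·(p1 − p0). Two-sided power at 5% is Φ[(d − 1.96·SE0)/SE1], where SE0 = √(2·p̄(1 − p̄)/35), p̄ is the mean observed risk, and SE1 = √([s·p0(1 − s·p0) + s·p1(1 − s·p1)]/35).

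Worked case, 10% v 30% with full recall: SE0 = √(2 × 0.2 × 0.8/35) = 0.0956; SE1 = √((0.09 + 0.21)/35) = 0.0926; (0.20 − 1.96 × 0.0956)/0.0926 = 0.14; power 55%.

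| Recall, both arms | 10% v 30%: difference, power | 20% v 40%: difference, power | 10% v 20%: difference, power |
|---|---|---|---|
| 100% | 20 points, 55% | 20 points, 45% | 10 points, 21% |
| 80% | 16 points, 45% | 16 points, 35% | 8 points, 17% |
| 60% | 12 points, 34% | 12 points, 25% | 6 points, 14% |
| 40% | 8 points, 23% | 8 points, 17% | 4 points, 10% |

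A count version agrees. Assume 0.6 v 0.3 events per child, so 21 v 10.5 events and a rate ratio of 2. Then SE of the log ratio = √(1/21 + 1/10.5) = 0.378, ln 2/0.378 = 1.83, power 45%. With 70%, 50% and 40% of events captured, the SE is 0.452, 0.535 and 0.598 and power is 34%, 25% and 21%.

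Both versions use all 35 children per arm. The plan's 15% loss would leave 35 × 0.85 = 29.75 and lower every power. The count version also assumes no overdispersion.

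**Step 4. Size and direction of unequal capture (illustration).** Take capture of 80% in one arm and 40% in the other.

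- Better capture in the exercise arm, no true difference (20% in both): observed 0.8 × 20% = 16% v 0.4 × 20% = 8%. An 8-point excess appears where there is none.
- Better capture in the control arm, true 20% exercise v 10% control: observed 0.4 × 20% = 8% v 0.8 × 10% = 8%. A true 10-point excess disappears.

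The direction therefore depends on which arm is better ascertained, which the documents do not determine.

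**The case against.** The strongest reply is that the text does not confine adverse-event questioning to week 12. The whole-study sentence comes after the timing rule and adds to it. The description of the calls does not say that bleeding is the only subject raised. The article is condensed and mentions protocol manuals, so a call script or adverse-event form may well exist. Bleeding, the disease-specific harm, is collected prospectively in both arms. In the exercise arm, many events would happen in front of the therapist.

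Much of this stands, and it rules out several stronger readings that a reader might infer:

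- *That the plan settles on one look-back question at week 12.* This is the literal reading of the timing rule, but the whole-study sentence prevents calling it settled. The text also does not say that the six-month interview covers adverse events.
- *That harm is undercounted, by some stated percentage.* No rate, recall fraction or source for recall loss is given. Any percentage loss in the observed difference simply restates the recall that was assumed.
- *That the error favours a conclusion of safety.* That requires equal forgetting in both arms. With therapist contact in one arm only, the error could also exaggerate harm.
- *That events will come to light too late to be acted on.* The supervised sessions make this unproven in the exercise arm.

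What does not stand is the view that this is only missing detail. The article is specific about the calls (recipients, timing, safety question, arm-specific reminder) and about the diary (content, duration). A procedure described that fully, and for bleeding alone, can be reviewed as written, and the two timing statements need reconciling in any case.

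A fair objection to the remedy is that a caller who gives the training reminder knows the allocation, so moving enquiry to the calls gives up some blinding.

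**Conclusion.** The point holds as a weakness in how a safety outcome is specified and collected. The Outcomes section gives two timing statements for adverse events that do not fit together, and names no regular contact at which both arms are asked about non-bleeding injuries. On the literal reading, these rest on open-ended recall over up to 12 weeks, so under-reporting is likely. Unequal therapist contact adds a risk of differential ascertainment in either direction.

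Its size cannot be derived from the documents. The illustrations show only that equal loss shrinks the absolute difference in proportion and that unequal loss can create or hide a difference. Even with full capture, power is 21% to 55% under the assumed rates, so better capture will not make this an adequately powered harms comparison. The gain is a more complete and comparable record of harms. The primary outcomes and the sample size are unaffected. The change is worth making because it is cheap.

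**What to change.** 1. Reconcile the timing rule with the whole-study sentence: list adverse events beside bleeding as an exception, and name the contacts at which they are asked about.
2. Add one scripted open-ended question to the existing weekly call in both arms, on any injury, pain or other health problem in the past week. Use identical wording and ask it before any training reminder.
3. Add an adverse-event line to the existing diary.
4. Keep the open-ended question put by the blinded assessor at week 12, to catch events not already reported.
5. Base the between-arm comparison on the sources common to both arms (calls, diary, week-12 question). Report events observed by the therapist separately.

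**Cost.** No new contacts or staff. Assuming about a minute per call, 70 children × 12 weeks = 840 calls, or about 14 hours in all; if calls run for the 16 weeks of bleed reporting, 70 × 16 = 1,120 calls, or about 19 hours. The downsides are more minor events to record and a caller who may know the allocation. Fixed wording, asking before the reminder, and the blinded week-12 question limit the second but do not remove it.

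### The weekly call that records bleeds also carries an exercise-only reminder, so the caller knows the arm, and adverse-event scope is stated in two ways: an avoidable risk of detection bias in the safety comparison

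*Protocol article*

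**What the plan says.** **Bleeds.** The end of the Background makes the frequency and severity of bleeding the secondary aim. Outcomes lists haemarthroses and intramuscular bleeds first among the secondary outcomes, self-reported over 16 weeks. On the calls it says that "participants in the intervention and control groups will be telephoned at the beginning of each week" and that "Participants in the both groups will be asked about bleeding episodes in the previous week". It then adds, for one arm: "In addition, participants in the intervention group will be reminded of their exercise training schedule". All children keep a bleed diary, and the final count combines diary and telephone data. Methods gives one definition of a bleed for the whole trial, based on the need for clotting factor.

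**Blinding.** Outcomes assigns the measurements after the 12-week program to an assessor unaware of allocation and names bleeding as the exception. The Abstract and Study design call the trial assessor-blinded, and the Discussion lists blind outcome assessment among the features that limit bias.

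**Adverse events.** Secondary outcome 5 takes events other than haemarthroses that are "associated with exercise or physical activity". After the paragraph's statement on timing and blinding, the scope is wider: "The number and type of any adverse effects that occur for the duration of the study" will also be recorded, again by open questions.

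**The concern.** There are two separate weaknesses, and both bear on the between-arm comparison of harm.

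First, one telephone call both collects an outcome and delivers part of the intervention's support. A caller who has to remind one child about training, and must not remind another, knows each child's arm when asking about bleeds. That knowledge can affect how far the caller probes, what is accepted as a bleed and how a vague answer is recorded. Families cannot be blinded to an exercise program, but the person asking the question can be.

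Second, if outcome 5 is what the arms are compared on, an event counts only once someone has linked it to exercise or activity. One arm trains under supervision twice a week, and Methods tells the other not to change its activity. The same sprain or sore knee is more readily put down to exercise in the first arm than in the second.

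At stake is the trial's evidence on whether exercise is safe in children with a bleeding disorder. A false signal of harm and a hidden real one are both possible. The three primary outcomes are not affected.

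**Working it through.** **The plan's own figure.** The only calculation in the article is the sample size, and it reproduces. A two-sided two-sample t-test for 0.75 SD with 80% power and α of 0.05 (two-sided assumed) needs 28.9, so 29 per group. Then 29 / (1 − 0.15) = 34.1, so 35 per group and 70 in all. Nothing below depends on it except the use of 35 per arm.

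**Bleeds: what is the same and what differs.**

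| Element | Exercise arm | Control arm |
|---|---|---|
| Call frequency | weekly | weekly |
| Bleed question | previous week | previous week |
| Diary | yes | yes |
| Bleed definition | common | common |
| Sources of final count | diary and telephone | diary and telephone |
| Training reminder in the call | yes | no |

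Only the last row differs, and it is enough to tell the caller the arm. Because telephone data enter the final count, that caller feeds the outcome directly.

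**Adverse events: the two statements side by side.** Outcome 5 requires a link to exercise or physical activity. The later sentence has no such condition and covers the whole study. The article does not say which set the arms are compared on. It does not say who asks, either; the calls are described as asking about bleeds only.

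**How large could an effect of unequal capture be?** The article gives no bleed rate and no capture probability, so every input here is assumed. With equal true rates, the observed rate ratio is capture in the exercise arm divided by capture in controls:

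- 95% v 85%: 0.95 / 0.85 = 1.12
- 95% v 80%: 0.95 / 0.80 = 1.19
- the same gaps reversed: 0.85 / 0.95 = 0.89 and 0.80 / 0.95 = 0.84

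The reversed figures are there because nothing in the article fixes the direction.

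**Effect on a test.** Assume Poisson counts, 35 children per arm and λ true bleeds per child over 16 weeks, with λ from 0.5 to 4. With capture d_E and d_C, the standard error of the log rate ratio is √[1/(35·λ·d_E) + 1/(35·λ·d_C)]. For λ = 1, d_E = 0.90 and d_C = 0.80:

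- expected counts: 35 × 0.90 = 31.5 and 35 × 0.80 = 28
- standard error: √(1/31.5 + 1/28) = 0.260
- ln(1.125) = 0.118, a shift of 0.118 / 0.260 = 0.45 standard errors
- chance that a nominal 5% two-sided test rejects: 7.4%

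| Assumed capture, exercise v control | Rate ratio, no true effect | Rejection at nominal 5%, λ from 0.5 to 4 |
|---|---|---|
| 90% v 90% | 1.00 | 5% |
| 90% v 80% | 1.125 | 6% to 15% |
| 90% v 70% | 1.29 | 10% to 46% |

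These figures show what unequal capture would do. They are not evidence that it will occur.

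**The case against.** The strongest reply is that the bleed data are collected in the same way in both arms. That is correct: frequency, question, recall period, diary and definition all match. A reader might infer from the reminder sentence that bleeds are ascertained by a different method in each arm, or that one arm is asked more often. The article does not support that. It supports only that the caller knows the arm.

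A second tempting inference concerns the therapist, who sees the exercise children twice a week and is trained to "understand the early management of a bleeding episode". A reader might conclude that this adds bleeds to one arm's count. But the final count draws only on diaries and calls, so the therapist is not a data source. Methods also says that all parents have been taught to recognise a bleed. Earlier recognition could equally bring forward treatment that would have been given anyway. This remains conjecture.

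Third, a reader might take it that the unblinded caller also gathers adverse events, or that only exercise-related events are recorded. Neither is stated. Bleeding is the only named exception to blinded measurement, and the wider adverse-event sentence already provides for recording without restriction. Outcome 5 also covers physical activity in general, which control children undertake too.

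Fourth, requiring clotting factor makes a bleed a fairly objective event, and the outcome is openly self-reported by families who know their arm, so a blinded caller removes only part of the risk. Detailed call scripts may well sit in the protocol manuals.

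All of this limits the point. What survives is what the article itself fixes: an arm-specific message inside the call that collects an outcome, and two adverse-event scopes that are not reconciled.

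**Conclusion.** The point holds as a risk of detection bias in the comparison of bleeds and harms, not as a demonstrated bias. It rests on reading the weekly call as a single call, as Outcomes describes it, and on the two adverse-event statements as printed. Size and direction are unknown. With no true effect, assumed capture of 95% against 85% or 80% would give a rate ratio of 1.12 or 1.19, and the reverse gap would give 0.89 or 0.84. It would be wrong to conclude that the safety comparison is biased, because the article establishes neither unequal capture nor its direction. The weakness touches secondary outcomes only, but one of them is the stated secondary aim, and the cause is avoidable. It is worth correcting because correction is cheap.

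**What to change.** 1. Take the training reminder out of the bleed call and give it to the exercise therapist, who already sees that arm.
2. Have the weekly bleed question asked from one fixed script in both arms by a caller who is not told the allocation. The sources of the bleed count can stay as they are.
3. State one adverse-event outcome for the between-arm comparison: all adverse events regardless of cause, elicited in the same way in both arms, with relation to activity as a coded field. Reword outcome 5 to match.

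The cost is call-script and form wording, reminders added to the therapist's work, and slightly more events to record. Sample size and treatment do not change. Families may still reveal their arm to the caller, so the risk is reduced, not removed.
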